### Clinical significance/ impact of the study

The current study can be helpful to identify whether kinesiophobia has any impact on the characterizes of patient with CLBP.The current study can be helpful to guide physician whether kinesiophobia be part of evaluation of patient with CLBP.

## Discussion

This study is to be conducted in Thumbay Physical Therapy & Rehabilitation Hospital which is equipped with all advanced equipment necessary for physiotherapy assessment associated with this study. Sample recruitment is expected to start from May 25, 2022, at Thumbay Physical Therapy & Rehabilitation Hospital, and Thumbay University Hospital and Gulf medical University, Ajman, United Arab Emirates.

Screening of individuals with and without chronic low back pain will be carried out by 4 experienced physiotherapists [2 males and 2 females] who are specialized in musculoskeletal and sports physiotherapy. In order to make the data collection uniform, all the therapists will be provided with the information about the study protocol including assessment methods using various assessment tools related to this study.

As per the medical record obtained on the prevalence of lower back pain conditions in Thumbay Physical Therapy & Rehabilitation Hospital and Thumbay University Hospital, we assume that the estimated sample size can be achieved within the study period given in the trial. Furthermore, the investigators of the study will contact the various departments of Thumbay University Hospital to refer the patients with and without low back pain to meet the sample required.

At least 80% of samples from the estimated sample size is anticipated for statistical analysis and reporting the study findings. Since the study covers a wide range of populations from various countries reporting to these medical centers, addressing confounding variables makes the study findings novel and generalizable.

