### Sample size

As for the calculation of the sample size, the odds ratio taken is 2 with the prevalence of 70% kinesiophobia [17] among CLBP patients and assumed the prevalence of 10% kinesiophobia among the controls, with the minimum required sample size of 600 [200 cases + 400 controls]. The case-control ratio taken is 1:2. The controls will be invited participants/patients who have no complaints of lower back pain at the Thumbay Physical Therapy & Rehabilitation Hospital, Ajman. All possible confounding factors will be controlled through subgroup analysis in later part during data analysis. The patients and controls will be identified from the outpatient clinic prospectively.

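### 600 is stated as the minimum required with no allowance for loss, yet the plan accepts as few as 480 in the analysis, so the required size may not be analysed

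*Protocol article*

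**What the plan says.** Protocol article, Sample size: the calculation ends "with the minimum required sample size of 600 [200 cases + 400 controls". Its inputs are "the odds ratio taken is 2 with the prevalence of 70% kinesiophobia" among CLBP patients, and the authors "assumed the prevalence of 10% kinesiophobia among the controls". On allocation the section says "The case-control ratio taken is 1:2". It gives no significance level, no power and no allowance for dropout or unusable data.

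Protocol article, Discussion: on recruitment, "we assume that the estimated sample size can be achieved within the study period given in the trial". The next paragraph adds "At least 80% of samples from the estimated sample size is anticipated for statistical analysis and reporting the study findings". It does not say why up to a fifth might be missing, or whether the shortfall would arise at recruitment or after enrolment.

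**The concern.** A required minimum is normally the number that must be available for analysis. If losses are foreseen, enrolment is set higher so that the minimum survives them. Here the minimum is also the recruitment target, and a later section accepts an analysis set up to 20% smaller. A reader cannot tell whether the study is sized on 600 or on 480.

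What is at stake is the power behind the stated size. The abstract bases its claim that the findings generalise partly on the sample being adequate. That adequacy has not been shown for the smallest analysis set the plan accepts.

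**Working it through.** **Inputs from the Sample size section.** Odds ratio 2; control prevalence p0 = 0.10; ratio r = 2 controls per case; stated size 200 + 400 = 600.

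**Input from the Discussion.** At least 80% of the estimated size analysed.

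**Assumptions, because the article gives neither.** Alpha 0.05 two-sided (z = 1.960) and power 80% (z = 0.842). The 1:2 ratio is assumed to hold in the analysed set.

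**1. Does 600 already contain a margin?**

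Case prevalence implied by odds ratio 2: p1 = 2 × 0.10 / (0.90 + 2 × 0.10) = 0.1818. Weighted mean: (0.1818 + 2 × 0.10) / 3 = 0.1273. Difference: 0.0818.

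- Pooled two-proportion formula, no continuity correction: cases = [1.960 × √(1.5 × 0.1273 × 0.8727) + 0.842 × √(0.1818 × 0.8182 + 0.10 × 0.90 / 2)]² / 0.0818² = 204.7, so 205 + 410 = 615.
- Simpler pooled (Kelsey) formula: cases = (1.960 + 0.842)² × 1.5 × 0.1273 × 0.8727 / 0.0818² = 195.3, so 196 + 392 = 588.

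The stated 600 lies between these two results, and neither includes inflation. On these inputs 600 is the number needed in the analysis.

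**2. The floor.** 0.80 × 600 = 480; 0.80 × 200 = 160 cases; 0.80 × 400 = 320 controls.

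**3. Power at each size.** Power = Φ[(0.0818 − 1.960 × SE0) / SE1], with SE0 from the pooled proportion and SE1 from the separate proportions.

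| Analysed | SE0 | SE1 | z | Power for odds ratio 2 |
|---|---|---|---|---|
| 200 + 400 | 0.02886 | 0.03113 | 0.811 | 79.1% |
| 160 + 320 | 0.03227 | 0.03480 | 0.534 | 70.3% |

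**4. Odds ratio detectable with 80% power.** Solving the same expression for the odds ratio with p0 = 0.10 gives 2.01 at 200 + 400 and 2.17 at 160 + 320.

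**5. Enrolment that would keep 600 at 80% usable.** 600 / 0.80 = 750 (250 + 500).

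**6. Sensitivity to the operative inputs.**

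- If 70% versus 10% is taken literally, the odds ratio is (0.70/0.30) / (0.10/0.90) = 21. Only about 21 to 33 subjects in total would be needed for 80% to 90% power, and power at 480 is close to 100%.
- If 70% is used as the reference prevalence with odds ratio 2 (82.4% versus 70%), two-sided 0.05, 90% power and a continuity correction, the result is exactly 200 + 400. This again has no inflation, but it moves the 70% away from the CLBP group to which the article assigns it. Without the correction, power falls from 91.8% at 200 + 400 to 84.7% at 160 + 320.

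**The case against.** Three counter-arguments have force.

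**The 80% is a floor.** The sentence says at least 80%, which includes 100%, and the same section expects the full number to be recruited and plans extra referrals to reach it. A reader might infer that only 480 are expected, that 600 will not be analysed, or that the two sections cannot both be true. The text supports none of these. An analysed number anywhere from 480 to 600 fits it. What stands is that the lower part of that range falls below the stated minimum and the article does not say so.

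**The calculation is under-specified.** Because alpha and power are missing, the reproduction is not unique, as the 70% reference-prevalence variant shows. A built-in 20% margin cannot be excluded by arithmetic: one-sided 0.05 with 80% power needs 163 cases, and 163 / 0.80 gives 204. Nothing in the article mentions such a margin, and calling 600 the minimum required speaks against it. The size of the power loss is therefore conditional; the lack of reconciliation is not.

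**Bias is not shown.** A reader might also infer that the missing fifth would be the most fearful patients, removed selectively by a complete-case analysis. The article gives no reason for the 80% and states no complete-case rule. CLBP patients must be able to perform the tests to be eligible, and unwilling patients are excluded. The sentence follows a paragraph on recruitment and may describe a recruitment shortfall. Handling of missing data may also lie in an analysis plan that is not shown. No claim of selective loss is made here.

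**Conclusion.** The point holds in a limited form. The article names 600 as its required minimum, states no allowance for loss, and accepts an analysis set as small as 480, so the required size may not be analysed. The two statements are unreconciled, not mutually exclusive.

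The loss at the floor is about nine percentage points of power (79.1% − 70.3% = 8.8). This rests on two-sided 0.05, odds ratio 2 with 10% in controls as the operative inputs, and a 1:2 ratio in the analysed set. It does not apply under 70% versus 10%. That those prevalences do not fit an odds ratio of 2 is a separate inconsistency, and it does not make 480 meet a stated minimum of 600.

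**What to change.** Reconcile the Sample size and Discussion sections, for example: *600 enrolled (200 cases, 400 controls); at least 480 (160 + 320) analysed, giving about 70% power for an odds ratio of 2, or 80% power for an odds ratio of about 2.17.* State the alpha, sidedness and power used, and say whether the 80% refers to recruitment or to usable data after enrolment. Do not present 600 as a minimum that the analysis will meet. If the operative prevalences turn out not to be those used here, recompute the figures before inserting them.

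The cost is a few lines of protocol text and a less favourable stated power. If the sponsor prefers to keep 600 as the minimum analysed, the enrolment consistent with 80% usable is 750 (250 + 500), which is 150 more participants.

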## Trail status

ClinicalTrials.gov Identifier: NCT05079893 Registered on 14/10/2021

## Data Availability

All authors will have access to the final trial dataset.
